### Data and safety monitoring board

A Data and Safety Monitoring Board (DSMB) and Protocol Steering Committee (PSC) will be established. The DSMB will consist of a statistician, an experienced HIV clinician and a cardiologist, without previous involvement in the trial. The DSMB will oversee the baseline coronary heart risk in study participants and provide advice as to whether the projected power of the study is likely to be achieved. Interim summary coronary heart risk data collected at the time of enrolment will be submitted to the DSMB after 25, 50 and 75 % of participants have been enrolled.

### Ongoing reporting

Doctors, other study site staff, coaches and moderators will record issues arising during the study in an issues log and report significant issues to the HealthMap study team within 24 h. The HealthMap study team will report all significant incidents to Human Research Ethics Committees within 72 h of the incident. All incidents will also be reported to the Protocol Steering Committee.

### Data analysis

All statistical analyses will be conducted using Stata 13 [54] according to the pre-specified plan below. All of the primary and secondary outcomes are measured at the individual level and therefore we will use Generalised Estimating Equations (GEEs) to allow for the clustering due to randomisation at the doctor level.

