### Sample size calculation

For the co-primary outcome of CHD risk, we used the primary dataset of STEAL (*n* = 280; [name], personal communication), a multi-site Australian HIV clinical trial [58] to estimate a geometric mean (due to skewed distribution) Framingham 10 year coronary heart disease risk [44] of 6.3 % units with standard deviation of 0.70 (log_e_ %units) and an intra-class correlation coefficient of 0.058. We then evaluated the Framingham 10 year coronary heart disease after we enrolled 563 participants. The geometric mean (due to skewed distribution) Framingham 10 year coronary heart disease risk was 6.9 % units with standard deviation of 0.72 (log_e_ %units) and an intra-class correlation coefficient of 0.09 (to account for the differences in CHD risk between the doctors). We estimated a minimum clinically important relative reduction of 24 % in Framingham risk based on similar effect sizes in previous self management [59] and cardiovascular risk management studies [60]. We conservatively estimated loss to follow up to the 12 month primary outcome as 15 %, five times the 96 week loss to follow up in the STEAL study [58]. Using clustersampsi in Stata (Version 12, College Station, TX, USA) and using a coefficient of variation of 1 (to account for the variation in the number of patients enrolled per doctor), we calculated that to provide 80 % power at a 5 % significance level (two-sided) we will require 60 doctors and a total sample size of 710 patients (355 per arm and an average 12 patients per doctor).

For the co-primary outcome of the Positive and Active Engagement in Life (PAEL), we used the primary dataset from an archived dataset held within Deakin University’s heiQ database. The most comparable intervention was selected from among hundreds of known interventions to match the likely impact of HealthMap. The dataset included *n* = 212 individuals who had an absolute mean gain in PAEL of 0.35 units with a standard deviation of 0.46 in the intervention group. Using clustersampsi in Stata (Version 12, College Station, TX, USA), a coefficient of variation of 1 for size of cluster and an intraclass correlation coefficient of 0.09, we calculated that to provide 80 % power at a 5 % significance level (two-sided) we will require 60 doctors and a total sample size of 142 patients (71 per arm and an average 2 patients per doctor). This sample size allows for a 15 % loss to follow up rate.

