### Examination of primary outcomes

The distribution of Framingham risk scores and PAEL are typically skewed, so scores will be log_e_ transformed where necessary. An estimate and 95 % confidence interval of the relative difference in geometric mean (at 12 months) between the intervention and control groups will be derived using linear regression, with adjustment for baseline scores and fitting using GEEs to allow for clustering by doctor.

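### Unless a small-sample correction is specified, GEE with 60 doctors of very unequal size would run at about 7 % type I error, not the planned 5 %

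*Protocol article*

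**What the plan says.** The Data analysis section of the protocol article names Stata 13, describes what follows as the pre-specified plan, and says "we will use Generalised Estimating Equations (GEEs) to allow for the clustering due to randomisation at the doctor level". For the primary outcomes (Examination of primary outcomes), the relative difference and its 95 % confidence interval come from "linear regression, with adjustment for baseline scores and fitting using GEEs to allow for clustering by doctor". Examination of secondary outcomes extends GEE to the continuous and binary secondary outcomes.

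The conditions under which this method must work are in Sample size calculation. The design is meant to give "80 % power at a 5 % significance level (two-sided) we will require 60 doctors and a total sample size of 710 patients", "using a coefficient of variation of 1 (to account for the variation in the number of patients enrolled per doctor", with the log-scale values updated during enrolment to "6.9 % units with standard deviation of 0.72 (log_e_ %units) and an intra-class correlation coefficient of 0.09".

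None of these sections states the working correlation, whether the standard error is robust or model-based, whether tests use a normal or a t reference, or any small-sample correction. None of these options is excluded either.

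**The concern.** GEE standard errors rest on large-sample theory, and the sample that has to be large is the number of clusters, not the number of patients. With 30 doctors per arm the usual standard error is biased downwards and a normal reference is slightly too liberal. Unequal cluster sizes make this worse. The sample size section allows for unequal sizes when it sets the number of patients, but nothing in the analysis sections carries that allowance into the inference.

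At stake is the error rate of the two primary comparisons. If the usual uncorrected form is used, their intervals are too narrow and a null result is declared significant more often than the plan's own 5 %. Leaving the estimator open also means that versions giving different p-values remain available at the time of analysis.

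**Working it through.** **1. The plan's own sample size, to confirm the inputs.** From Sample size calculation: "We estimated a minimum clinically important relative reduction of 24 % in Framingham risk"; SD 0.72 on the log scale; ICC 0.09; CV 1; 15 % loss ("We conservatively estimated loss to follow up to the 12 month primary outcome as 15" per cent); average 12 patients per doctor, so about 10 analysed (12 × 0.85 = 10.2).

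- Effect on the log scale: |ln 0.76| = 0.274.
- Individually randomised n per arm: 2 × 0.72² × (1.96 + 0.842)² / 0.274² ≈ 108.
- Design effect: 1 + ((1 + CV²)m − 1) × ICC = 1 + (2 × 10 − 1) × 0.09 = 2.71.
- Analysed n per arm: 108.05 × 2.71 ≈ 293, or 29.3 doctors at 10 each, rounded up to 30.
- Total recruited: 2 × 30 × 10 / 0.85 = 706, against 710 stated.

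The stated figure reproduces. With 355 × 0.85 ≈ 302 analysed per arm, power is 81.0 % with a normal reference and 79.7 % with t on 58 degrees of freedom.

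**2. Type I error of the GEE test.** Trials were simulated with no intervention effect: 60 doctors, 1:1 allocation stratified by cluster size, mean 10 analysed patients per doctor, CV 1, ICC 0.09, and a linear GEE on arm and baseline. Three assumptions are not in the document: gamma-shaped cluster sizes, a residual ICC of 0.09 after baseline adjustment, and a baseline slope of 0.7 with a normal outcome on the analysis scale. Each row below is based on 24,000 trials; the Monte Carlo standard error is √(0.067 × 0.933 / 24,000) ≈ 0.16 points.

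| Working correlation | Standard error and reference | Type I error |
|---|---|---|
| Exchangeable | Robust, normal | 6.7 % |
| Exchangeable | Model-based, normal | 6.8 % |
| Exchangeable | Robust, t | 6.2 % |
| Exchangeable | Kauermann-Carroll, t | 5.7 % |
| Exchangeable | Mancl-DeRouen, t | 5.1 % |
| Independence | Robust, normal | 7.6 % |
| Independence | Kauermann-Carroll, t | 6.1 % |
| Independence | Mancl-DeRouen, t | 5.1 % |
| Exchangeable, equal cluster sizes | Robust, normal | 6.0 % |

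Separate simulations on the same inputs gave 6.6-6.8 % (robust) and 6.6-7.1 % (model-based) for the uncorrected exchangeable form, and 4.8-5.1 % for Mancl-DeRouen with t.

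**3. Size of the standard error bias.** The mean robust standard error was 0.95 of the true value with exchangeable correlation and 0.93 with independence. Coverage of a nominal 95 % interval is 100 − 6.7 = 93.3 % and 100 − 7.6 = 92.4 % respectively.

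**4. Sensitivity.** Runs of 8,000 trials varied the ICC from 0.02 to 0.09, the CV from 0.6 to 1.5, mean size from 10 to 12, and the presence of the baseline covariate. The robust standard error with a normal reference gave 6.5-7.9 %. Mancl-DeRouen with t gave 4.9-5.6 %.

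**5. Source of the excess.** Equal clusters already give 6.0 %, so the number of doctors accounts for about 1 point. The CV of 1 adds about 0.7 points under exchangeable correlation (6.7 − 6.0).

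**The case against.** The strongest objection is that the article never says the uncorrected form will be used. It names a class of model and no estimator. The variance estimator and degrees of freedom are details that an article commonly leaves to an SAP, and the SAP is not shown. This stands. A reader might infer that the stated method has a 7 % error rate, or that the plan contradicts its 5 % level; the text does not support either, because the relevant choice is not stated. The point remains more than a request for detail, because both usual ways of computing the standard error, with a normal reference, miss the plan's own level under the plan's own inputs.

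A reader might also blame a few very large doctors. That overstates the mechanism. Under exchangeable correlation a doctor's weight is about m / (1 + (m − 1) × ICC). For m = 10 this is 10 / 1.81 = 5.5, and it can never exceed 1 / 0.09 = 11.1, so even the largest doctor counts about twice an average one. Unequal sizes add to the problem but do not create it.

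The planning ICC describes risk at enrolment, whereas the analysis adjusts for baseline, so the residual ICC is unknown. That is a fair limit on precision. It does not remove the result: at an ICC of 0.02 the robust, normal-reference error was 7.9 %.

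Finally, the excess is modest, and nothing here was shown for the logistic GEE analyses. Both remarks are correct.

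**Conclusion.** The point holds in conditional form. If the GEE analyses use an uncorrected standard error and a normal reference, the two-sided type I error on the plan's own 60 doctors, CV of 1 and ICC of 0.09 is about 6.6-7.1 % with exchangeable working correlation. It is about 7.6 % with independence and a robust standard error. That is an excess of roughly 1.5-2.5 points, with nominal 95 % intervals covering about 92-93 %. The main causes are the limited number of doctors and, on top of that, their unequal sizes.

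Confidence in the figures is high for continuous outcomes under the assumptions listed. Whether the trial will actually use the uncorrected form cannot be settled from the article. Stratification by doctor type was not simulated, and no claim is made for the binary outcomes.

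**What to change.** Unless the SAP already does so, state for the two primary outcomes and the other continuous GEE analyses:

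- an exchangeable working correlation within doctor;
- the Mancl-DeRouen bias-corrected robust variance;
- t critical values with degrees of freedom equal to doctors minus doctor-level parameters, here about 60 − 2 = 58.

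This restores about 5 %. The Kauermann-Carroll correction should not be offered as interchangeable, since with t it still gave 5.7-6.1 %. If Stata 13 does not provide the chosen correction, name the software that will be used.

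The change is to analysis wording only and does not touch recruitment or data collection. Intervals become roughly 5-10 % wider than the uncorrected ones. Power for the coronary risk outcome, from the sample size formula with a t reference, is about 79.7 %, so the 80 % claim is essentially kept. The wording should be settled before anyone sees outcome data by arm.

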### Examination of primary outcomes

The distribution of Framingham risk scores and PAEL are typically skewed, so scores will be log_e_ transformed where necessary. An estimate and 95 % confidence interval of the relative difference in geometric mean (at 12 months) between the intervention and control groups will be derived using linear regression, with adjustment for baseline scores and fitting using GEEs to allow for clustering by doctor.

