### Randomisation procedures

Cluster randomisation will be performed at the level of treating doctor by a statistician, after stratification for doctor type (general practitioner versus physician) and number of enrolled patients (above and below median). Doctors will be randomly assigned 1:1 to either immediate (intervention arm) or deferred (control arm) access to the intervention package. Random allocation will be performed using the ‘ralloc’ program in the statistical package Stata 13 [54].

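### The primary and continuous secondary GEE models leave out the randomisation strata, so reported standard errors may be somewhat too large

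*Protocol article*

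**What the plan says.** Under Randomisation procedures, the protocol article allocates doctors 1:1 "after stratification for doctor type (general practitioner versus physician) and number of enrolled patients (above and below median"). Two binary factors give four strata of doctors.

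Under Data analysis, it says the analyses will be run "according to the pre-specified plan below". Examination of primary outcomes then names the model for both co-primary outcomes, with scores log-transformed where necessary: "linear regression, with adjustment for baseline scores and fitting using GEEs to allow for clustering by doctor". Neither stratification factor appears. Examination of secondary outcomes adjusts the continuous outcomes for their baseline measure where there is one, and names no covariates for the binary outcomes.

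The Sample size calculation takes no credit for stratification or for baseline adjustment.

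**The concern.** Stratified allocation keeps the arms alike on doctor type and enrolment volume, so differences between strata largely cancel out of the treatment comparison. A model without the strata does not know this. It leaves between-stratum variation in the residual doctor-level variance, and the reported standard error includes variation that the design has already removed.

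Doctor-level variance is a large part of the uncertainty here. With the planning values (SD 0.72 on the log scale, ICC 0.09, CV of cluster size 1, about 10 evaluable patients per doctor), it makes up about two thirds of the variance of the treatment difference before baseline adjustment. A doctor-level factor that explains a good share of it could visibly change the interval that the trial reports. The article gives no reason for balancing on the two factors and then leaving them out of the model.

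**Working it through.** **Inputs from the Sample size calculation.** Relative reduction 24 %, so δ = |ln 0.76| = 0.2744; SD 0.72; ICC 0.09; CV 1; loss to follow-up 15 %; 60 doctors; 710 patients; two-sided 5 %; 80 % power.

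**Step 1: reproduce the stated size.**
- Before clustering: n = 2 × [0.72 × (1.960 + 0.842) / 0.2744]² ≈ 108.05 per arm.
- Evaluable patients per doctor: m = 12 × 0.85 = 10.2.
- Design effect: 1 + [(CV² + 1)m − 1] × ICC = 1 + 19.4 × 0.09 = 2.746.
- 108.05 × 2.746 ≈ 297 per arm, or 350 after dividing by 0.85. The total is 700, which is 1.4 % below 710.
- Power at 710 with 15 % loss (301.75 per arm, m = 10.06): 81.0 % by the normal approximation, 79.7 % by t with 58 df.

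The stated size reproduces without any reference to the strata.

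**Step 2: planning formula with strata.** Let s be the share of between-doctor variance that the strata explain. The article gives no value, so s is an assumption. Between-doctor variance is 0.72² × 0.09 = 0.0467 and within-doctor variance is 0.72² × 0.91 = 0.4717. The SE is √{2[0.4717 + 0.0467(1 − s) × 2m] / 301.75}.
- s = 0: 0.0967. The doctor-level share is 0.0467 × 20.12 / 1.410 ≈ 0.67.
- s = 0.25: 0.0883. s = 0.50: 0.0790.

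With the strata omitted, the test still uses about 0.0967, but the estimate varies by roughly the smaller figure. Power is then Φ[(0.2744 − 1.96 × 0.0967) / true SE]: 81 % at s = 0, 83 % at s = 0.25 and 86 % at s = 0.50. Leaving the strata out therefore does not push power below the planned level. With the strata in the model, the same formula gives 87.5 % and 93.5 %. It ignores baseline adjustment and weights all patients equally, so it does not describe the model in the plan.

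**Step 3: simulation of the model in the plan.** 60 doctors, mean 10 evaluable patients, CV about 1, exchangeable GEE with robust SE, 1,500 runs per scenario, baseline correlation assumed to be 0.5.

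| s | Strata | True SE | Reported SE | Type I error | Power |
|---|---|---|---|---|---|
| 0.25 | out | 0.0712 | 0.0738 | 4.6 % | 96.3 % |
| 0.25 | in | 0.0710 | 0.0696 | 6.2 % | 96.9 % |
| 0.50 | out | 0.0651 | 0.0727 | 3.7 % | 97.3 % |
| 0.50 | in | 0.0646 | 0.0636 | 6.1 % | 98.9 % |

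- Ratio of reported SEs, out to in: 0.0738 / 0.0696 = 1.06 and 0.0727 / 0.0636 = 1.14. At s = 0 it is 1.00; at an extreme s = 0.75 it is 1.25.
- Reported against true SE with strata out: 0.0738 / 0.0712 = 1.04 and 0.0727 / 0.0651 = 1.12.
- Reported against true SE with strata in: 0.0696 / 0.0710 = 0.98 and 0.0636 / 0.0646 = 0.98. This is slightly too small, which is why type I error exceeds 5 %. Across the scenarios with s from 0.25 to 0.75 it ran from 5.3 % to 6.8 %, with only a K/(K − p) correction.
- Interval around a ratio of 0.76 at s = 0.50: 0.76 × exp(±1.96 × 0.0727) gives 0.66 to 0.88; 0.76 × exp(±1.96 × 0.0636) gives 0.67 to 0.86.
- Other baseline correlations at s = 0.50: power is 91.9 % against 94.6 % at correlation 0, and 100.0 % either way at 0.8.

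The simulation error of a 5 % rejection rate is √(0.05 × 0.95 / 1500) = 0.56 points. So 4.6 % cannot be told from 5 %, while 3.7 % lies 2.3 simulation errors below it. Part of each power gap comes from the liberal test in the adjusted model, so the gaps are upper readings.

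**The case against.** Four points can be made for leaving the plan as it is.

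First, this is a condensed article, and a statistical analysis plan that is not shown may include the strata. That is possible. But the article does not merely stay silent: it presents its text as the pre-specified plan and names the adjustment. If another document adds the strata, the two need reconciling.

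Second, the baseline score may already carry whatever the strata predict. This stands. Nothing in the article shows that doctor type or enrolment volume predicts the 12-month outcome given baseline, and if they do not, nothing is lost.

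Third, the error is on the safe side, and adjustment without further care moves type I error above 5 %. This also stands, and it shapes the fix.

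Fourth, adding covariates to a logistic model changes the odds ratio being estimated, not only its precision. This stands for the binary outcomes.

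A reader might infer that the benefit of stratifying is lost altogether, or that the trial is underpowered. The documents do not support either reading. Balance by design still reduces the variability of the estimate, whichever model is fitted, and the 710 patients were calculated without credit for the strata. Setting 81.0 % against 93.5 % from the planning formula would also mislead: it treats the estimate as if it varied by the inflated standard error, and it ignores the baseline adjustment that the plan specifies.

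**Conclusion.** The point holds in a limited form. The stated covariate set departs from the randomisation scheme, and the consequence is confined to the reported standard error, interval and test. The true SE hardly differs (0.0651 against 0.0646 at s = 0.50), and the planned power is intact. False positives are not inflated by the omission.

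For an assumed 0 %, 25 % or 50 % of between-doctor variance explained, the reported SE is about 0 %, 6 % or 14 % larger without the strata. With an assumed baseline correlation of 0.5, power at the target effect is about 0.6 points (25 %) to 1.6 points (50 %) lower. These sizes rest on two quantities that the article does not give: the prognostic strength of the strata and the baseline correlation. The mismatch in the text is certain; the size of its effect is not. It is worth correcting because the change is small, not because the trial's conclusions are at risk.

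**What to change.** In Examination of primary outcomes, and for the continuous outcomes in Examination of secondary outcomes, add doctor type (general practitioner or physician) and enrolment stratum as fixed covariates. Use the stratum recorded at randomisation, not one recalculated from final enrolment. In the same sentence, specify a small-sample correction of the robust standard error (for example Mancl-DeRouen) with t critical values, because with 60 doctors the adjusted model can otherwise exceed 5 % type I error. The two changes belong together. If the strata are deliberately left out, say why.

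For the binary outcomes, adding the strata is optional. If they are added, state that the odds ratio is then conditional on them.

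The cost is a short change of wording, 2 doctor-level degrees of freedom, and the added correction. No new data are needed, since both factors are known for every doctor at randomisation, and the sample size does not change.

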### Examination of secondary outcomes

For the continuous secondary outcomes measured at the six and/or 12 month visit: coronary heart risk (relative to age and as estimated by HIV-specific risk score); fasting total cholesterol and total cholesterol: HDL ratio; systolic blood pressure; body mass index and waist circumference; and quality of life and mental health status scores; an estimate of the absolute mean difference (or relative difference in geometric means for outcomes with a lognormal distribution) and 95 % confidence interval between the intervention and control groups will be derived by linear regression using GEE (to account for clustering by doctor) with adjustment for, where applicable, baseline measures of the secondary outcome.

For the binary secondary outcomes measured at the 12 month visit: smoking status (smoker versus non-smoker); achievement of Australian cardiovascular risk factor management targets (yes versus no); HIV virus suppression (yes versus no); and achievement of HIV quality of care measures (yes versus no); an estimate of the Odds Ratio (OR) and 95 % confidence interval for the intervention compared to the usual care will be derived by logistic regression modelling using GEEs, to allow for clustering by doctor. To identify latent HR-QoL and self-management profiles at baseline, Latent Profile Analysis will be conducted using MPlus software package (ref). Associations between latent profiles at baseline and both demographic characteristics and change on binary secondary outcomes will be identified. This approach will allow intervention responsiveness to be explored within the context of baseline self-management practices and functioning.

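### The latent profile analysis is said to let intervention responsiveness be explored, but as described it compares no arms within profile (minor, exploratory)

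*Protocol article*

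**What the plan says.** All of the relevant text is in one paragraph of the protocol article, *Examination of secondary outcomes*. The *Data analysis* section introduces it as part of the pre-specified plan.

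- **Main model for binary outcomes.** An odds ratio "for the intervention compared to the usual care will be derived by logistic regression modelling using GEEs, to allow for clustering by doctor". This has an arm effect and no profile term.
- **Profiles.** "To identify latent HR-QoL and self-management profiles at baseline, Latent Profile Analysis will be conducted using MPlus software package".
- **Use of the profiles.** "Associations between latent profiles at baseline and both demographic characteristics and change on binary secondary outcomes will be identified".
- **Inference attached.** "This approach will allow intervention responsiveness to be explored within the context of baseline self-management practices and functioning".

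The binary outcomes are smoking status, achievement of Australian risk-factor targets, HIV virus suppression and achievement of HIV quality-of-care measures. No other section describes an interaction, subgroup or effect-modification analysis. The randomised comparison that such an analysis would need does exist: "Doctors will be randomly assigned 1:1 to either immediate (intervention arm) or deferred (control arm) access to the intervention package" (*Randomisation procedures*).

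**The concern.** Responsiveness to an intervention is a contrast between arms, and differential responsiveness is how that contrast varies across profiles. The described step relates profile to change and names no arm. The article then says that this approach allows responsiveness to be explored, which does not follow.

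Patients in different profiles can change at different rates for reasons unrelated to the intervention. Their prognosis differs, and extreme baseline values tend to move back towards the average. With a binary outcome, the room to change also depends on baseline status: only a baseline smoker can become a non-smoker. All of this occurs in both arms. It remains if the analysis is confined to the intervention arm, because nothing is then left to subtract it.

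At stake is the reading of one exploratory result. A profile could be described as more responsive when it merely has a different outlook, or a real difference in effect could be overlooked.

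**Working it through.** **Figures in the plan.** The article gives no figure for the profile analysis, so there is none to reproduce. The trial size, used only to set the scale below, does reproduce. The inputs, from *Sample size calculation*, are a "minimum clinically important relative reduction of 24 % in Framingham risk", a "standard deviation of 0.72 (log_e_ %units) and an intra-class correlation coefficient of 0.09", a cluster-size coefficient of variation of 1, 15% loss, and an average of 12 patients for each of 60 doctors.

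- Individually randomised, 80% power, two-sided 5%: 2 × [0.72 × (1.960 + 0.842) / |ln 0.76|]² ≈ 108, or 109 per arm as computed by the sample-size routine.
- Analysed patients per doctor: 12 × 0.85 = 10.2.
- Design effect: 1 + [(1² + 1) × 10.2 − 1] × 0.09 = 2.746.
- Total: 2 × 109 × 2.746 / 0.85 ≈ 704, against 710 stated.

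**What each association estimates.** For one binary outcome, write

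logit P = β0 + β1·arm + β2·profile + β3·arm×profile.

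- Profile log odds ratio in the control arm: β2 (prognosis, including regression to the mean).
- Profile log odds ratio in the intervention arm: β2 + β3.
- Difference between the two, which is differential response: β3.

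The intervention-arm association equals β3 only if β2 = 0. With β2 = ln 2 and β3 = 0 it is an odds ratio of 2 with no differential response. The pooled association is a blend of β2 and β2 + β3, and does not isolate β3 either.

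**Simulation of the same point.** It used 60 doctors with 10 analysed patients each, two equally common profiles, control-arm log odds of −1 in the reference profile, a doctor random-effect SD of 0.5 on the logit scale, 1,000 replicates, and logistic regression with cluster-robust standard errors. The outcome was 12-month binary status. Everything except the number of doctors and the approximate cluster size is an assumption. The figures are rejection rates at 5%.

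| Scenario | Profile association, pooled | Arm-by-profile interaction |
|---|---|---|
| No treatment effect; profile prognostic (OR 2) | 96.7% | 5.5% |
| Treatment OR 1.5 in both profiles; prognostic OR 2 | 97.0% | 3.8% |
| Treatment OR 2 in one profile, 0.5 in the other | 3.1% | 97.0% |

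The third row is built so that the pooled association cancels. With β1 = β2 = ln 2 and β3 = −ln 4, the log odds in control and intervention are −1 and −0.307 in one profile, and −0.307 and −1 in the other. It shows that the association can miss a reversal of effect entirely, not that it usually will.

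**Precision of the alternative.** Ignoring clustering, with two equal profiles, equal arms and similar outcome rates, the variance of the arm effect is proportional to 2/(N/2) = 4/N, and that of the interaction to 4/(N/4) = 16/N. The interaction's standard error is therefore √(16/4) = 2 times as large. More profiles, or unequal ones, make it worse.

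**The case against.** The strongest reply is that the article gives a three-sentence sketch and no model for this step: no regression type, no covariates, no statement about arm. A journal article may leave such detail to a full plan. The sentences follow directly on the intervention-versus-usual-care model, and the stated aim is responsiveness to the intervention, so an analysis by arm may well be what is meant. The text also promises only exploration and attaches no test or decision. Finally, the simulation assumes that arm is left out and then shows that a main effect is not an interaction, which is textbook knowledge.

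Much of this stands. A reader might infer that the protocol has chosen an arm-blind analysis or excluded an interaction. It has not, and a fuller plan may contain one. A reader might also infer that the article claims to demonstrate responsiveness, which it does not. The simulation illustrates the logic and is not evidence about this trial's data.

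What the reply does not remove is the link between the two sentences. The article names a specific analysis and says that this approach serves a specific purpose. Followed as written, it does not. That is a stated method that does not match its stated aim, which is more than an omitted detail.

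**Conclusion.** The concern holds in a limited form. As described, the profile–change association includes no comparison of arms within profile and cannot by itself inform responsiveness. It concerns one exploratory secondary analysis, leaves the primary conclusions untouched and changes no stated number. The algebra needs no assumption about this trial; the percentages depend on the assumed settings and only show that the confusion can be near-complete in either direction.

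Three stronger readings are tempting and are not supported:

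- **That the result would misdirect who is later offered the model.** No section uses profiles to allocate anything. The whole deferred arm is offered the model after the trial (*Study design*), and coaching is directed at smokers and those above a cardiovascular-risk threshold (*Component 3*).
- **That the bias can be sized from regression to the mean on the Positive and Active Engagement in Life score.** That score is continuous and is not an outcome of this analysis, and the article gives no test–retest correlation from which to compute it.
- **That restricting the step to binary outcomes is an error.** Nothing in the article contradicts it; it is a choice of scope.

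**What to change.** Add one sentence to *Examination of secondary outcomes*. For each binary secondary outcome, arm, baseline profile and their interaction will be fitted in the doctor-clustered GEE logistic model, adjusting for the baseline value of the outcome where available. Arm odds ratios within profile will be reported with the interaction estimate and 95% confidence interval, all labelled exploratory. If this is not wanted, delete the sentence on responsiveness and present the profile associations as descriptive.

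The cost is wording only: the data are already to be collected and the model is already planned. The downside is imprecise interaction estimates, so a null interaction should not be read as equal effect across profiles.

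Extending the analysis to the two primary outcomes, and carrying uncertainty in profile membership into the model, are optional.
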